### Clinical monitoring and bio-sampling protocol

Enrolled patients will be monitored every 3–4 months for a total period of 12 months. On each visit, routine laboratory, serological (C3/C4, anti-dsDNA) and urine tests will be performed, and disease activity will be quantified by the validated indices: a) SLE Disease Activity Index-2000 (SLEDAI-2K)^26^ and b) Physician Global Assessment (PhGA; scale 0–3).^27^ For the detection and quantification of flares, the SELENA-SLEDAI Flare Index (SFI) will be employed,^27^ following minor modifications as outlined in **Table 1**. Patient history, physical examination and any relevant laboratory or imaging tests will be considered to exclude any flare-mimics such as infection or drug adverse effect. Administered medications and dosages will be recorded.

**Table 1. T1:** Modified SELENA-SLEDAI Flare Index.^27^

**Moderate flare**	**Severe flare**
Increase in SLEDAI by ≥3 points (but not to >12)	Increase in SLEDAI to >12 points
New or worse: discoid, photosensitive, profundus, cutaneous vasculitis or bullous lupus rash, nasopharyngeal ulcers, serositis, arthritis, fever	New/worse: neurological lupus, vasculitis, nephritis, myositis, platelet <60.000/μL, haemolytic anaemia (Hb <7 g/L or ↓ Hb > 3 g/L)
Increase or added prednisone, but to a dose <30 mg/day	Increase or added prednisone to a dose ≥30mg/day, or pulses of intravenous methylprednisolone
Added NSAID or antimalarials (for SLE activity)	Added cyclophosphamide, azathioprine, methotrexate or mycophenolate, or new biological drugs (rituximab, belimumab) for SLE activity, or hospitalization
Increase in PhGA by ≥1 (but not to >2.5)	Increase in PhGA to >2.5

SLEDAI, SLE disease activity index; NSAID, nonsteroid anti-inflammatory drugs; PhGA, physician global assessment; Hb, haemoglobin.

Upon inclusion to the study, all patients will donate a first blood sample (15 ml) obtained by venipuncture (low disease activity/remission stage). During follow-up, a second blood sample will be obtained from two SLE patients who will develop moderate or severe flare according to the SFI (flare stage). Those patients will be managed for active disease at the discretion of the treating physician and in line with the EULAR recommendations.^28^ Three months after therapeutic intervention of the flare, a third blood sample will be collected (post-flare stage).

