## BACKGROUND AND STUDY RATIONALE

One of the intriguing characteristics of Systemic Lupus Erythematosus (SLE) is its tendency for increases in disease activity, also known as flares, which are often unpredictable. Indeed, in various patient cohorts, the frequency of SLE flares (or relapses) is approximately 0.30–0.50 per patient-year, and despite available treatments, long-term disease quiescence occurs only in a small fraction of patients.^1^ The clinical burden of lupus flares is remarkable, since about 30–40% of exacerbations affect multiple or major organs (for instance, kidneys), they necessitate treatment escalation or switch (including administration of high-dose glucocorticoids or other potent immunosuppressives), and are linked to almost 2-fold increased risk for irreversible organ damage.^2,3^ Importantly, treatment of SLE relapses remains empirical due to lack of randomised evidence and personalised options based on the underlying pathophysiology.

The cellular and molecular mechanisms implicated in SLE re-activation following a previous period of quiescence remain elusive.^4^ During recent decades, the advent of next-generation genome sequencing technologies coupled with focused cellular immunology studies, have provided unique insights regarding the role of specific cell types of both innate (eg, neutrophils) and adaptive (eg, follicular helper T-cells, long-lived plasmablasts) immunity as well as of pertinent pathways (eg, interferon-alpha, autoantibodies) in SLE pathogenesis.^5–10^

To this end, the gene expression and functional state of cells may be altered under the effect of exogenous or other (for instance, inflammatory cytokines) factors through epigenetic changes including histone and chromatin modifications.^11,12^ In fact, changes in the epigenetic and transcriptional program of tumour-surveilling immune cells have been linked to resistance to chemotherapy and progression of malignant disease.^13,14^

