### Sample size

Considering that single-cell technologies enable the profiling of thousands of individual cells (up to 10,000 cells per sample) from peripheral blood samples, a relatively small number of patients is adequate. Since this is a pilot study, only two (2) patients will be analysed, each patient sampled on three consecutive time points: during remission or low disease activity, at the time of flare, 3 months post-flare and after treatment administration.

Patient samples of each time point will be combined and profiled in a separate 10x Multiome library. To identify two eligible patients, a total 20 SLE patients who meet the aforementioned inclusion criteria will be monitored clinically over a period of 12 months.

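### Table 1 gives both haemoglobin limits for haemolytic anaemia in g/L: as printed, one can never be met and the other lies within ordinary visit-to-visit variation

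*Protocol article*

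**What the plan says.** The protocol article, under Clinical monitoring and bio-sampling protocol, makes the modified index in Table 1 the operative flare definition: "For the detection and quantification of flares, the SELENA-SLEDAI Flare Index (SFI) will be employed". Among the new or worse manifestations in the severe column is "haemolytic anaemia (Hb <7 g/L or ↓ Hb > 3 g/L". The unit appears twice, the same both times, and is not stated or corrected elsewhere. Haemolytic anaemia has no entry in the moderate column.

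The index decides who is sampled at flare: "a second blood sample will be obtained from two SLE patients who will develop moderate or severe flare according to the SFI (flare stage". Next to it stands a clinical safeguard: history, examination and relevant tests "will be considered to exclude any flare-mimics such as infection or drug adverse effect".

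On the schedule, the same section says "Enrolled patients will be monitored every 3–4 months for a total period of 12 months". Under Sample size, "a total 20 SLE patients who meet the aforementioned inclusion criteria will be monitored clinically over a period of 12 months", in order to find the two who are analysed.

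**The concern.** The two limits do not fit together in the printed unit. One asks for almost no haemoglobin at all; the other asks for a change of a few per cent. Two limits joined by an 'or' in one severity item should mark roughly comparable degrees of illness, and these do not.

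What is at stake is the definition of the flare stage. The study contrasts inactive, flare and post-flare samples in two patients, so the flare rule decides which patients supply the contrast. A limit that cannot be met adds nothing to that rule, and a limit met by small fluctuations does not separate mild from severe haemolysis. Because haemolytic anaemia is listed only as a severe item, the unit can also decide whether a patient with slight new haemolysis and no other qualifying feature counts as flaring at all.

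**Working it through.** The plan states no calculation for these limits, so there is no figure to reproduce. The check converts the units and then asks how often a stable patient would meet the printed fall.

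**Inputs from the protocol article:** limits of 7 g/L (absolute) and 3 g/L (fall), from Table 1; visits every 3–4 months for 12 months; 20 patients monitored and 2 analysed.

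**Assumptions, because the article gives neither:** usual haemoglobin 110–140 g/L; total within-person CV 1–4%; two readings from a stable patient differ by a normally distributed amount with mean zero. The table does not say which earlier value the fall is measured from; one pair of visits is used here.

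**Step 1: units.** 1 g/dL = 10 g/L, so 7 g/L = 0.7 g/dL and 3 g/L = 0.3 g/dL.

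**Step 2: absolute limit.** 7/140 = 5.0% and 7/110 = 6.4% of the assumed haemoglobin. Even from 110 g/L, a patient would have to lose 110 − 7 = 103 g/L. Anyone who did so would long since have passed the 3 g/L fall, so the absolute limit is redundant as well as unattainable.

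**Step 3: fall limit.** 3/140 = 2.1% and 3/110 = 2.7% of the assumed haemoglobin. For a stable patient:

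SD of the difference = √2 × CV × Hb, and P(fall > 3) = 1 − Φ(3 / SD).

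Example at Hb 110 and CV 2%: SD = 1.414 × 0.02 × 110 = 3.11 g/L; 3/3.11 = 0.96; P = 0.167.

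| CV | SD of difference, Hb 110 to 140 (g/L) | P(fall > 3 g/L), Hb 110 to 140 |
|---|---|---|
| 1% | 1.56 to 1.98 | 0.027 to 0.065 |
| 2% | 3.11 to 3.96 | 0.167 to 0.224 |
| 3% | 4.67 to 5.94 | 0.260 to 0.307 |
| 4% | 6.22 to 7.92 | 0.315 to 0.352 |

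**Step 4: scale across the cohort.** At one visit pair, the expected number of 20 stable patients with such a fall is 20 × P: about 0.5 to 1.3 at CV 1%, and 3.3 to 7.0 at CV 2–4%. The schedule allows roughly 12/4 = 3 to 12/3 = 4 follow-up visits per patient, so there is more than one opportunity.

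**Step 5: the same digits per decilitre.** The limits become 70 g/L and a fall of 30 g/L. That fall is 30/140 = 21% to 30/110 = 27% of the assumed haemoglobin, and over the whole CV range its chance probability is at most 7.6 × 10⁻⁵ per visit pair. In this unit both limits describe a large departure, so they are coherent with each other. This shows coherence; it does not show what the cited index says.

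**The case against.** The strongest reply is that the haemoglobin figures do not stand alone. They are a bracket after haemolytic anaemia, under a heading that requires a new or worse manifestation. A patient who drifts from 128 to 124 g/L without haemolysis does not meet the item on its natural reading. The clinical exclusion of mimics is a second barrier: infection and drug effects are only its examples, and the wording covers any mimic.

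This stands, and it limits the consequence. A reader might infer that a trivial fall in haemoglobin labels a patient as a severe flare, so that 17–35% is a false-flare rate and half the flare data is at risk. The article does not support that. The relevant event is a small fall in a patient who also has new or worse haemolytic anaemia and passes the clinical review, and the article gives nothing from which to estimate it.

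Other points also carry weight. Moderate and severe flares both trigger the sample, so a wrong grade alone does not change who is sampled. Genuine flares should not be scarce: the background section says "the frequency of SLE flares (or relapses) is approximately 0.30–0.50 per patient-year", which for 20 patient-years is 20 × 0.30 = 6 to 20 × 0.50 = 10. Clinicians used to the index would probably recognise the slip. And this is one item among many in the severe column of a two-patient, non-interventional pilot.

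None of this makes the limits right. If haemolysis has to be shown separately, the figures are there to grade it, and in the printed unit they do not: one is never met, and the other is met by almost any fall.

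**Conclusion.** Wrong as written. The haemoglobin limits in Table 1 cannot do their job in g/L: the absolute limit is out of reach, and the fall limit lies within ordinary variation. How far within depends on the assumed CV: about 3–7% of visit pairs in a stable patient at 1%, and about 17–35% at 2–4%, for haemoglobin of 110–140 g/L. These figures are the chance of meeting the printed number and nothing more.

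The unit error is plain from the table itself and needs no outside source. That the intended unit is g/dL is an inference from the coherence of the two figures, because the cited index is not at hand. The effect on the study is probably small, but it cannot be quantified from the article. The point still matters because the faulty item sits in the rule that selects the only two patients analysed.

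**What to change.** Reconcile the haemoglobin unit of both limits in Table 1 with the index that the table cites, and correct the table accordingly. The per-decilitre reading should be confirmed against that source before it is adopted. If a flare form or checklist has been derived from the table, carry the same correction into it; the article does not describe one. The cost is a one-line change to the table plus a check of any derived form. Design, visits and sample size are unaffected.

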### Isolation of peripheral blood mononuclear cells and single-cell RNA-seq/ATAC-seq

We will assay blood as a relevant and easily accessible tissue to define complex inflammatory signatures.^29,30^ Venous samples (2 patients x 3 time-points, 6 in total) will undergo Ficoll density centrifugation for isolation of peripheral blood mononuclear cells (PBMCs). In SLE, the PBMCs fraction also includes circulating neutrophils,^31^ which are relevant to disease pathogenesis. Single-cell suspensions will be prepared on microplates through the robotic Fluidigm C1 system, followed by purification of RNA and chromatin from the cell nuclei.^32^ Genomic material will be processed for library synthesis (DNA for chromatin, cDNA for gene expression) and analysis by the chromium-based (10x) single-cell multiome ATAC (Assay for Transposase-Accessible Chromatin) & gene expression.^32–34^ Next-generation sequencing will be carried out at the Genomic Facility, IMBB-FORTH.

### Bioinformatics and data analysis

We will create a single-cell transcriptomic and epigenomic atlas followed by modularity optimisation to detect immune cell clusters across patient groups and time-points.^35,36^ Differential gene expression between pertinent immune cell clusters, coupled with functional enrichment analysis, will characterise the cellular states and dedicated transcriptional programs predisposing to flares. Chromatin accessibility data will help to disentangle the regulatory programs governing the transition to active SLE, guided by the cell-to-cell linkage between modalities (scRNA-seq, scATAC-seq) and the cell-state annotations of the transcriptome atlas. Using the scATAC-seq data, we will characterise our immune cell clusters, and determine high resolution cell sub-clusters with unique chromatin accessibility profiles. Open chromatin regions (OCRs) will be subjected to functional enrichment analysis (LOLA, GREAT tools) to infer their putative regulatory roles.^37,38^ Also, mapping of transcription factor (TF) binding sites (TFBS) motifs^39^ will reveal enrichment of specific TFs involved in the acquisition of a primed state of immune cells. Correlation between gene expression, TF expression and motif accessibility will identify flares-predisposing Gene Regulatory Networks (TF-to-gene promoter/enhancer relationships). Finally, reconstruction of immune cell lineage differentiation and cell maturation trajectories will delineate the cellular dynamics and underlying states during SLE re-activation*.*^35,40^ Collectively, our analysis will decipher how gene regulatory reprogramming in immune cells triggers flare initiation. We will also test the reversibility of these molecular/regulatory programs in the post-flare samples.

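### Only patients who flare are sequenced, so the analysis can describe what accompanies a flare but cannot identify what predisposes to it or triggers it

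*Protocol article*

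**What the plan says.** Who is assayed is fixed in three places in the Methods of the protocol article.

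- Under *Sample size*: "only two (2) patients will be analysed, each patient sampled on three consecutive time points". To find them, "a total 20 SLE patients who meet the aforementioned inclusion criteria will be monitored clinically over a period of 12 months".
- Under *Clinical monitoring and bio-sampling protocol*: at inclusion "all patients will donate a first blood sample (15 ml) obtained by venipuncture (low disease activity/remission stage". Later, "a second blood sample will be obtained from two SLE patients who will develop moderate or severe flare according to the SFI (flare stage". A third sample follows three months after the flare is treated.
- Under *Isolation of peripheral blood mononuclear cells*: "Venous samples (2 patients x 3 time-points, 6 in total) will undergo Ficoll density centrifugation".

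What will be concluded is stated in *Bioinformatics and data analysis*. Differential expression between cell clusters, with enrichment analysis, "will characterise the cellular states and dedicated transcriptional programs predisposing to flares". Correlating gene expression, transcription factor expression and motif accessibility is to identify gene regulatory networks that predispose to flare. The section then sums up: "Collectively, our analysis will decipher how gene regulatory reprogramming in immune cells triggers flare initiation". It closes with a test of whether the programs reverse in the post-flare samples.

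**The concern.** Predisposition is a statement about the quiescent state: a feature predisposes to flare if it is more frequent, or stronger, in quiescent patients who go on to flare than in those who do not. To see that, the outcome must vary among the patients whose remission samples are profiled. Here every profiled patient flares by selection. Whatever is found in the two remission samples may be a property of quiescent lupus at large.

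The second sample does not repair this. It is taken once a moderate or severe flare has been recognised, so a change between remission and flare may be a cause of the flare, a consequence of it, or something that runs alongside. A trigger cannot be singled out from that contrast.

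At stake is what the study may report. If the analysis section is followed as written, a difference between remission and flare in two patients would be published as a predisposing program or a triggering mechanism, and might be taken up as a candidate for predicting or preventing flare.

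**Working it through.** **Inputs**

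| Input | Value | Source (protocol article) |
|---|---|---|
| Patients analysed | 2, three time points each | Sample size |
| Selection | both have a moderate or severe flare | Clinical monitoring and bio-sampling |
| Samples processed | 6 | Isolation of mononuclear cells |
| Baseline blood | drawn from every enrolled patient | Clinical monitoring and bio-sampling |
| Cohort | 20 patients, 12 months | Sample size |
| Flare rate | 0.30–0.50 per patient-year | Background and study rationale |
| Cells per patient sample | at least 3,000 to 5,000 | Aims of the study |
| Profiling capacity | up to 10,000 | Sample size |

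**1. The plan's own figure.** 2 patients x 3 time points = 6 samples. Reproduced.

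**2. Comparators for predisposition.** Patients sequenced minus flarers sequenced = 2 − 2 = 0. For 2 flarers and k non-flarers, the smallest exact one-sided permutation p at patient level is 1/C(2+k, 2). With k = 0 it is 1/C(2, 2) = 1: the contrast does not exist. More cells per sample do not change this, because they add neither patients nor a second outcome.

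**3. What each available contrast can show.**

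- Remission against flare, same patient: what changes by the time a flare is present.
- Flare against post-flare, same patient: what reverses after treatment.
- Remission in future flarers against remission in non-flarers: what predisposes. Not available.

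**4. Would the cohort contain non-flarers?** Assume a constant hazard, the same for all patients, and no dropout. Expected flare-free at 12 months = 20 x exp(−rate).

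- Rate 0.30: 20 x exp(−0.30) = 14.8 flare-free, 5.2 flaring.
- Rate 0.50: 20 x exp(−0.50) = 12.1 flare-free, 7.9 flaring.

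So about 12 to 15 of the 20 would be flare-free. The 18 patients who are not sequenced are not 18 non-flarers: 5.2 − 2 = 3.2 to 7.9 − 2 = 5.9 of them would be expected to flare too. Finding two flarers is likely: the binomial probability of at least 2 among 20 is 0.980 at rate 0.30 and 0.999 at rate 0.50.

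**5. What adding non-flarer baselines could buy.** Each library pools the samples of one time point, so a fair comparator belongs in the remission library. Assume that one library yields 10,000 nuclei shared equally, and that 10–30% are lost at quality control. The article states neither.

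| Non-flarers added (k) | Smallest one-sided p, 1/C(2+k, 2) | Nuclei per sample, 10,000/(2+k) | After 10–30% loss |
|---|---|---|---|
| 0 (as planned) | 1 | 5,000 | 4,500–3,500 |
| 1 | 1/3 = 0.333 | 3,333 | 3,000–2,333 |
| 2 | 1/6 = 0.167 | 2,500 | 2,250–1,750 |
| 3 | 1/10 = 0.100 | 2,000 | 1,800–1,400 |
| 5 | 1/21 = 0.048 | 1,429 | 1,286–1,000 |

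One comparator already brings the yield to or below 3,000 after loss, and two bring it below 3,000 before any loss. Spreading three non-flarers over the three libraries keeps 3,333 per sample, but two of the three would then differ from the flarers' remission samples by library as well as by outcome. The smallest p would still be 1/10.

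**The case against.** **It is a pilot, and each patient is their own control.** The article calls the study a pilot. Three samples per patient, including a reversibility test, carry real within-patient information, and the idea of primed cells can be read as a within-patient one. This stands as a defence of the small sample and of a descriptive analysis. It does not defend the unqualified claims about predisposition and triggering.

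**The full protocol or analysis plan may deal with it.** It may well specify models and filters. But the article itself fixes the assayed set at two flarers and six samples, and no analysis can recover a contrast with no data on one side.

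**Much of the article is more careful.** The stated aim is to investigate the basis of flares. The anticipated-results section speaks of populations altered during flare and of transcriptomes associated with re-activation, and says only that biomarkers could emerge. This stands, and it confines the point largely to the claims in the analysis section.

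**A reader might infer more: that stored samples of non-flarers lie idle and that sequencing a few would make *predisposing* legitimate.** The documents do not support this. They say that every patient donates baseline blood. They do not say that non-flarers' cells are kept, and processing is described for six samples only. Because the flarers are unknown at inclusion, some holding of baseline material is implied until a flare occurs, but no more than that. A condensed article that describes no use does not show that there is none. Nor would the comparison settle the matter. Every participant must have relapsing-remitting disease, so 12 flare-free months do not show absence of predisposition, and a comparator may flare later.

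**Conclusion.** The point holds as a mismatch between the stated conclusions and the assayed set. With two sequenced patients, both flarers, and zero non-flaring comparators at remission, the study can describe changes that accompany flare and their reversal after treatment. It cannot identify predisposing programs, predisposing networks or a trigger. This follows from the article's fixed text and rests on no numerical assumption.

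The figure of about 12 to 15 flare-free patients of 20 is indicative only. It assumes a constant hazard and no dropout, and takes its rate from general cohorts rather than from the selected patients recruited here (relapsing-remitting, history of anti-dsDNA, currently quiescent). It shows that potential comparators are likely to exist, not that their cells are available.

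It would be too strong to conclude that the study's aim as a whole fails. A descriptive pilot of the transition into and out of flare remains feasible.

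**What to change.** **Needed.** In *Bioinformatics and data analysis*, replace the three claims (programs that predispose, networks that predispose, reprogramming that triggers) with association with the transition to flare or the flare state. Label the results hypothesis-generating. This matches the restrained language already used in the anticipated-results section. Cost: wording only; no change to recruitment, sampling or sequencing.

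**Optional and exploratory.** If baseline cells of participants who stay flare-free for 12 months have been kept, profile one or more of them in the same library as the flarers' remission samples. State beforehand that the comparison involves two flarers, that nuclei per sample may fall to or below 3,000, and that a comparator may flare later. Cost: cell processing, separation of donors within the pool, possibly more sequencing, and a wait until flare-free status is known. The result could suggest features for a later study. It would not by itself restore the word *predisposing*.

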## AIMS OF THE STUDY

In this research study, we aim to investigate the cellular and molecular basis of flares in patients with SLE. Considering the complexity of the disease, we will utilise state-of-the-art single-cell sequencing technologies to obtain a detailed map of the transcriptional and epigenetic profiles in multiple subtypes of peripheral blood immune cells. Through a prospective biosampling protocol, we plan to simultaneously characterise gene expression and chromatin accessibility at single-cell resolution in the peripheral blood mononuclear cells (at least 3,000 to 5,000 cells per patient sample) from two (2) SLE patients assayed at three (3) consecutive time points: disease remission, flare and post-flare (after treatment modification). Our hypothesis is that specific epigenetic modifications (chromatin accessibility) direct the molecular reprogramming of specific immune cells thus contributing to SLE relapse.

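### Reversibility is judged on the samples that define the programs, and the third sample is timed by therapy, so partial reversal or persistence can arise from noise or treatment

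*Protocol article*

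**What the plan says.** The Aims section plans "two (2) SLE patients assayed at three (3) consecutive time points: disease remission, flare and post-flare (after treatment modification"). The section on isolation of mononuclear cells fixes the material: "Venous samples (2 patients x 3 time-points, 6 in total) will undergo Ficoll density centrifugation". Under Sample size, "Patient samples of each time point will be combined and profiled in a separate 10x Multiome library", so time point and library coincide.

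The Bioinformatics section describes clustering across time points, differential expression between cell clusters, motif enrichment and regulatory networks, all aimed at programs that predispose to flare. It then adds: "We will also test the reversibility of these molecular/regulatory programs in the post-flare samples". It names neither the contrast that selects a program nor the comparator for reversal.

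Under Clinical monitoring, "a second blood sample will be obtained from two SLE patients who will develop moderate or severe flare according to the SFI". On treatment: "Those patients will be managed for active disease at the discretion of the treating physician". On the last sample: "Three months after therapeutic intervention of the flare, a third blood sample will be collected (post-flare stage"). No clinical response is required for that sample. The same section records SLEDAI-2K, PhGA and medications at visits but states no use of them in the reversibility analysis.

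**The concern.** Two separate problems meet in one analysis.

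The first is selection. A program that stands out between remission and flare does so partly through true change and partly through chance error in those two samples. Each patient has only one of each. Any comparison of the post-flare sample with either of them uses again a value whose error helped to select the program, and that error does not recur in the post-flare sample. Regression to the mean then looks like a biological result.

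The second is what the third sample represents. It follows a treatment change and carries no condition on disease state. A fall in a program may be resolution of the flare or a direct drug effect on cell numbers or expression. Failure to fall may be a persistent program or simply a patient who is still active.

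The article hopes for biomarkers of remission and exacerbation and for targetable pathways. Reversal after the flare is a natural argument that a program is linked to the flare, so a biased reversal measure would feed directly into those claims.

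**Working it through.** **1. The plan's own figure.** 2 patients × 3 time points = 6 samples, as stated. Each patient therefore has one remission value (R), one flare value (F) and one post-flare value (P) per feature. The document gives no alpha, effect size or SD, so every shift and SD below is an assumption.

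**2. Algebra with no true change.** Let R, F and P be independent with equal mean and variance σ².

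- Var(F−R) = Var(F−P) = 2σ² and Cov(F−R, F−P) = σ², so the correlation is 0.5.
- Hence E[F−P | F−R = d] = d/2, and by symmetry E[P−R | F−R = d] = d/2.

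On average the post-flare value sits halfway, whatever σ is.

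**3. Size with no true change.** Select features with z = (F−R)/(σ√2) > 1.96. The mean z of those selected is 0.05844/0.025 = 2.338.

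- Share with P < F: approximately Φ(0.5 × 2.338/√0.75) = Φ(1.35) = 0.912. Simulation with 4 million features gives 90.8%.
- Rejection by a nominal one-sided 5% test of F > P: approximately 1 − Φ((1.645 − 1.169)/0.866) = 1 − Φ(0.55) = 0.291. Simulation gives 29.5%.
- Mirror test of P > R (not returned): the direction is right in 90.7% and the test again rejects 29.5%.
- At least 80% reversal is seen in 21% of selected features, and at most 20% reversal also in 21%.

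The bias therefore has no fixed direction. The comparator decides it.

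**4. Size with a true shift that fully persists (true reversal 0%).** Simulation: 20,000 features, two patients averaged, a true shift in 3% of features, top 600 selected by |F−R|. Apparent reversal = 1 − (P−R)/(F−R). The last column assesses the same features on fresh remission and flare samples.

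| Assumed shift | Assumed SD | Apparent reversal, selecting samples | Fresh samples |
|---|---|---|---|
| 1.0 | 0.25 | 8% | 0% |
| 0.5 | 0.25 | 37% | 0% |
| 1.0 | 0.5 | 37% | 0% |
| 0.5 | 0.5 | 48% | 7% |
| 1.0 | 1.0 | 48% | 1% |
| 0.5 | 1.0 | 50% | 13% |
| none (top 500) | any | 50% | not defined |

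Only the ratio of shift to SD matters: a ratio of 2 gives 37% twice and a ratio of 1 gives 48% twice. The 7% and 13% in the last column are ratios with small denominators. Rows with the same ratio (7% and 1%) differ only by simulation error. Profiling more cells does not help, because the noise that matters lies between samples.

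**5. Assessing in the other patient.** With no true change, selecting in one patient and checking direction in an independent second patient gives 49.7%, which is chance.

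**6. Pooling by time point.** If half of the noise variance is shared within a library (an assumption), the correlation across patients is 0.5 × 0.5 = 0.25. The expected share is Φ(0.25 × 2.338/√0.9375) = Φ(0.604) = 0.727; simulation gives 72.6%. With one library per time point, the cross-patient check loses part of its protection.

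**7. The third sample.** No arithmetic applies. The eligibility criteria exclude rituximab in the previous 6 months and cyclophosphamide in the previous 3 months, so neither exposure is recent at the first sample. Table 1 lists cyclophosphamide, "or new biological drugs (rituximab, belimumab) for SLE activity" among the features of a severe flare, and the third sample comes three months after treatment. The first and third samples can therefore differ in drug exposure as well as in disease state.

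**The case against.** The document does not say that programs are selected on flare versus remission. It speaks of differential expression between clusters, motif enrichment and networks, and a condensed article may leave the definition of reversal to a fuller plan. That stands, and the missing definition is not the point here. The point is that with one sample per patient per stage, whichever comparator is chosen within a patient shares a sample with the selection.

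Treatment is also part of what the third time point is said to measure, and a non-interventional study cannot standardise it. That stands for change on treatment. It does not license reading the change as return to quiescence. Whether a drug that depletes a cell type will be given is unknown.

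This is also one secondary analysis in a two-patient pilot with cautious promises, which limits the importance of the point but does not remove the bias.

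Three stronger readings are tempting and not supported:

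- A reader might infer that the study would report reversibility even if no program were linked to flare. The comparator is not stated, and the same noise favours persistence equally. The 91% and 29% are per-feature figures under pure noise, not the chance of a false study conclusion.
- A reader might infer that LLDAS and DORIS are measured at the third sample. They are entry criteria; the listed follow-up measures are SLEDAI-2K, PhGA and the flare index.
- A reader might infer that rewording the analysis is enough. Uncoupling library from time point changes the laboratory layout.

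**Conclusion.** The concern holds in limited form. If programs are selected on the flare versus remission difference, a within-patient reversibility test is biased: towards reversed against flare, and towards persistent against remission. Noise produces partial movement, about half on average when nothing truly changes. When a true shift fully persists, apparent reversal runs from 8% (shift four times the SD) to 50% (shift half the SD). These sizes rest on assumed shifts and SDs, equal noise at each stage and independent samples.

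Separately, and without any assumption about selection, the third sample cannot distinguish return to quiescence from treatment effect in two patients on unstandardised therapy. The analysis should be changed, but neither problem invalidates the atlas itself.

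**What to change.** 1. **Select in one patient, assess in the other, and vice versa.** Report the post-flare position relative to the second patient's own remission and flare values, averaged over the selected features. Do not screen features again on the second patient's flare difference, since that brings the bias back. If the program does not rise at flare in the second patient, say that reversal cannot be assessed.
2. **Library layout.** Where feasible, spread time points over the same three pooled libraries, for example one patient's remission sample with the other's flare sample and the reverse. A library artefact in the flare difference then has opposite signs in the two patients. Crossing six samples over three libraries does not remove library effects, so they still need a caveat. If time points stay in separate libraries, state that shared library effects can mimic reversal even in the cross-patient check.
3. **Report by clinical state and treatment at the third sample.** Use the recorded SLEDAI-2K and PhGA, LLDAS or DORIS where derivable, and recorded medication. Call the result on-treatment change when quiescence is not regained, and flag cell types directly depleted by a drug received.
4. **Call the result descriptive.**

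Cost: items 1, 3 and 4 change the analysis text only. Item 2 changes pooling but not the number of samples or libraries. The downside is fewer and weaker reversal claims, possibly none.
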